## Abstract

**Background:**

Older adults in nursing home and home-care are a particularly high-risk population for weight loss or poor nutrition. One negative consequence of undernutrition is increased health care costs. Several potentially modifiable nutritional risk factors increase the likelihood of weight loss or poor nutrition. Hence a structured and multidisciplinary approach, focusing on the nutritional risk factors and involving e.g. dieticians, occupational therapists, and physiotherapist, may be necessary to achieve benefits. Up till now a few studies have been done evaluating the cost-effectiveness of nutritional support among undernourished older adults and none of these have used such a multidisciplinary approach.

**Methods:**

An 11 week cluster randomized trial to assess the cost-effectiveness of multidisciplinary nutritional support for undernutrition in older adults in nursing home and home-care, identified by screening with the Eating validation Scheme. Before start of the study there will be performed a train-the-trainer intervention involving educated nutrition coordinators.

In addition to the nutrition coordinator, the participants assigned to the intervention group strategy will receive multidisciplinary nutrition support. Focus will be on treatment of the potentially modifiable nutritional risk factors identified by screening, by involving physiotherapist, registered dietician, and occupational therapist, as relevant and independent of the municipality’s ordinary assessment and referral system.

The primary outcome parameter will be change in quality of life (by means of Euroquol-5D-3L). Secondary outcomes will be: physical performance (chair stand), nutritional status (weight, Body Mass Index and hand-grip strength), oral care, fall incidents, hospital admissions, rehabilitation stay, moving to nursing homes (for participants from home-care), use of social services and mortality.

An economic evaluation will be conducted to evaluate the cost-effectiveness of the multidisciplinary support.

Furthermore, interviews with nursing home and home-care management, nursing staff and nutrition coordinators in both the control and intervention groups, participants in the intervention group and the involved multidisciplinary team will be performed.

**Conclusion:**

In this study we will evaluate in a randomized controlled trial whether multidisciplinary nutritional support is cost-effective, in undernourished older adults in home-care and nursing home and contribute to important research.

**Trial registration:**

ClinicalTrials.gov 2013 NCT01873456.

## Background

Older adults in nursing home and home-care are a particularly high-risk population for weight loss or poor nutrition
[1]. In Denmark as many as 50% of older adults in nursing homes suffer from unintended weight loss and, app. 20% of the residents and 12% of the clients have a body mass index (BMI) below 18.5
[2, 3].

The negative consequences of undernutrition, i.e. increased risk for morbidity and mortality, impaired cognitive, physical, and social function and hence reduced quality of life, and increased health care costs, hospital stays, more general practitioner visits, more intensive nursing care, increased requirement of nursing home-care etc.
[1]. The increased need for care and social services leads to costs of billions of euro’s every year
[1]. A Dutch study showed extra cost for managing nursing home residents at risk of undernutrition at 8.000 euro per nursing home resident and 10.000 Euro for undernourished residents
[4]. And a Danish, Swedish and a Norwegian study have shown that older adults in respectively, nursing homes and home-care, who are undernourished, need more assistance with Activities of Daily Living (ADL) than older adults who are in good nutritional status and due to that, may add to the substantial and costly burden of care
[3, 5, 6].

Several potentially modifiable nutritional risk factors increase the likelihood of weight loss or poor nutrition
[7, 8]. Even though there is increasing evidence that the use of oral nutritional support (ONS) among nursing home residents improves weight and reduces mortality
[9], the evidence for a benefit among older adults in home-care is very limited
[9]. In addition, a much more structured and multidisciplinary approach, focusing on the significant modifiable nutritional risk factors and involving e.g. dieticians, occupational therapists, physiotherapist, may achieve additional benefits. Recently, we therefore developed and validated a nutritional risk screening tool, Eating Validation Scheme (EVS), which is designed for use among nursing home residents and home-care clients and includes eating habits, recent weight loss and the potentially modifiable nutritional risk factors, eating dependency, leaves 25% or more of food uneaten at most meals, chewing and swallowing problems with the aim of using these information in a multidisciplinary approach as needed
[10]. The plan is to implement EVS all over Denmark. However, the EVS has only been tested in a small unpublished pilot study, including a train-the-trainer intervention and nutrition coordinators. However the results need to be confirmed by a proper randomized controlled trial, where the benefits of a multidisciplinary nutritional intervention aimed at residents and clients, who are identified by means of EVS, are assessed.

According to a recent systematic review, there is actually published some such multidisciplinary intervention among undernourished adults
[11]. Unfortunately the 15 studies included in the systematic review had reported very few relevant outcomes and it was therefore not possible to conclude if multidisciplinary interventions were effective
[11]. Only two of the studies included in the systematic review were performed among nursing home residents (and none among home-care clients). One of these actually documented a positive effect nutritional and functional status of a multidisciplinary intervention consisting of energy- and protein dense home-made oral supplements, exercise and oral care
[12]. While the other found that a multidisciplinary intervention consisting of education of nutrition coordinators including train-the-trainer sessions were able to maintain nutritional status
[13].

Up till now a few studies have been done evaluating the cost-effectiveness of nutritional support among frail older adults. Recently these studies were summarized in a systematic review
[14]. The authors concluded that the use of nutritional support, mainly in the form of ONS or enteral feeding nutrition in the management of undernutrition could be efficient from a health economic perspective
[14]. Two of the studies included in the review were performed among nursing home residents and home-care clients. However, none of the studies included in the review used a multidisciplinary approach. It could be expected that such a multidisciplinary approach would be accompanied by higher health care costs than usual care, due to the additional staff and assistance of physiotherapist, registered dietician, occupational therapist, etc. But it could also be expected that these higher costs are negligible compared with increased quality of life and the cost-savings this can potentially generate.

The aim of this study is to assess the cost-effectiveness of multidisciplinary nutritional support for undernutrition in older adults in nursing home and home-care.

## Methods

### Design

This study is designed as an 11 week cluster randomized controlled trial assessing the benefits of a new model for multidisciplinary nutritional support. The protocol has been send to the Danish Ethical Board which has concluded that approval is not needed and that the project can be carried on as described.

Older adults are eligible for this study when they are 65+ years old and achieve 2 points in the EVS (see below)
[10].

The primary outcome parameter will be change in quality of life (by means of Euroquol-5D-3L, see below). Secondary outcomes will be: physical performance (chair stand), nutritional status (weight, BMI and hand-grip strength), oral care, fall incidents, hospital admissions, rehabilitation stay, moving to nursing homes (for participants from home-care), use of social services and mortality.

An economic evaluation will be conducted alongside the randomized trial to evaluate the cost-effectiveness of the multidisciplinary support.

Furthermore, interviews with nursing home and home-care management, nursing staff and nutrition coordinators in both the control and intervention groups, participants in the intervention group and the involved multidisciplinary team will be performed.

### Feasibility of recruitment and sample size

Unpublished results have shown that around 25% of nursing home residents will achieve 2 points in the EVS. According to our knowledge no nutritional support studies among nursing home residents and home-care clients have used Euroquol-5D-3L. However in a study of multidisciplinary nutritional support among another frail group of older adults, patients with hip fractures, Hoekstra and co-workers
[15] used this measure and found a significant difference between intervention and control group in the Euroquol-5D-3L follow-up score of 0.145 (p = 0.004). Hence, with a statistical significance level of 0.05 and a power of 80% two groups of 65 older adults is calculated to be sufficient. The above mentioned unpublished study found that it was possible to screen 600 nursing home residents during an 8 weeks period.

Taking into account an expected loss to follow up of 10% during the 11 weeks of intervention based on a former multidisciplinary study among nursing home residents
[12], and estimating equal findings among home-care clients, we aim to include a total of 145 older adults with 2 points in EVS. We therefore need to screen about 600. This number could probably be reached in approximately 8 weeks.

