### Weaknesses

We have chosen to include participants with 2 points in EVS, instead of using e.g. the Mini Nutritional Assessment (MNA), which might limit the comparability with other studies. The reason for choosing EVS is that this tool, in contrast to e.g. the MNA is developed and validated in order to identify older adults in home-care and nursing home, who could benefit from nutritional support. However, whether this is actually true has never been examined before
[10].

The participants included in the study should be able to complete the planned tests and to give informed consent. These criteria might exclude demented and functionally impaired persons and hence reduce the representativeness of our findings.

Furthermore, according to our knowledge, there have only been performed a few randomized controlled studies of nutritional support among home-care clients and none using a multidisciplinary approach.

Finally the EQ-5D-3L has apparently not been used in this population before. Hence our expectations about feasibility of recruitment and sample size assessment are based on relatively few published data, primarily among nursing home residents. However we expect that the home-care population is less frail than the nursing home population and therefore may be more willing to participate.

In relation to this, we have decided to use cluster randomization to avoid contamination. Hence the estimated sample may be too small to detect a significant difference
[25]. Due to limited time and resources it is not possible to increase the number of clusters. To try to compensate for this we aim to include statistical analysis of the percentage of individuals in the different clusters that benefits.

We could have decided to use the Short Physical Performance Battery (SPPB) for the functional assessment. SPPB measures chair rise, balance and gait speed. However instead we decided to use methods which we had experience working with from former studies, and which gives some of the same information as the SPPB, i.e. 30 seconds chair-stand and RAI.

We have decided to use quality of life as our primary outcome. Another relevant outcome measure could have been ADL, especially since former studies have shown that older adults in respectively, nursing homes and home-care, who are undernourished, need more assistance with ADL than older adults who are in good nutritional status and due to that, may add to the substantial and costly burden of care

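### The stated 80% power with 65 per group comes from an individually randomised calculation; with six clusters it is lower, and the added percentage-that-benefits analysis cannot restore it

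*Protocol article*

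**What the plan says.** Protocol article, Feasibility of recruitment and sample size: the target is taken from a hip-fracture study that reported a "difference between intervention and control group in the Euroquol-5D-3L follow-up score of 0.145 (p = 0.004"). From this the section concludes that "with a statistical significance level of 0.05 and a power of 80% two groups of 65 older adults is calculated to be sufficient". The only inflation follows: "Taking into account an expected loss to follow up of 10% during the 11 weeks of intervention", which leads to 145 participants. No SD, ICC or design effect appears.

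Design and Randomization: the trial is cluster randomised, with three nursing-home clusters and three home-care clusters.

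Weaknesses: after giving cluster randomisation as the reason, the article says "Hence the estimated sample may be too small to detect a significant difference". It adds that more clusters are not possible, and continues: "To try to compensate for this we aim to include statistical analysis of the percentage of individuals in the different clusters that benefits".

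**The concern.** The Methods present 80% power as a property of this trial. The calculation behind it treats the 130 evaluable participants as independent, whereas the design allocates six groups of them. The Discussion concedes the problem but does not quantify it, leaves the Methods statement unchanged, and offers a remedy that does not act on the cause.

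The stake is interpretation. Anyone who takes 80% at face value will give a non-significant result more weight against the intervention than the design can bear. Anyone who accepts the compensation sentence will think the shortfall has been dealt with.

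**Working it through.** **Inputs from the article.** Difference 0.145; alpha 0.05; power 80%; 65 per group; 10% dropout; 145 to include; six clusters.

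**Inputs assumed, because the article does not give them.** Two-sided test; three clusters per arm, equal in size; SD back-solved from the article's own claim; ICC from 0 to 0.10.

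**Step 1: the plan's own figures.** A two-sample t-test with 65 per arm and 80% power needs a standardised effect of 0.495. The implied SD is 0.145/0.495 = 0.293 (0.295 with the normal formula). So 65 per group fits an individually randomised comparison at that SD, but it cannot be confirmed independently, since no SD is stated. Dropout: 130/(1 − 0.10) = 144.4, rounded up to 145. Dropout explains the whole step from 130 to 145, so that step contains no allowance for clustering.

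**Step 2: add clustering.** Analysed per cluster: m = 65/3 = 21.7. Design effect: DE = 1 + (m − 1) × ICC. Standard error of the difference: SE = 0.293 × √(2 × DE/65). Power is computed from 0.145/SE in two ways: with a normal reference, which applies the design effect only, and with a non-central t on 6 − 2 = 4 degrees of freedom (critical value 2.776), which is a t-test on cluster means. The last column is the difference detectable with 80% power on 4 df, 3.76 × SE.

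| ICC | DE | SE | Power, design effect only | Power, 4 df | Detectable difference, 4 df |
|---|---|---|---|---|---|
| 0 | 1.00 | 0.051 | about 80% | 57% | 0.19 |
| 0.01 | 1.21 | 0.056 | 73% | 50% | 0.21 |
| 0.02 | 1.41 | 0.061 | 66% | 44% | 0.23 |
| 0.05 | 2.03 | 0.073 | 51% | 33% | 0.28 |
| 0.10 | 3.07 | 0.090 | 36% | 24% | 0.34 |

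**Step 3: could more participants repair it?** With three clusters per arm, SE cannot fall below 0.293 × √(2 × ICC/3) however large the clusters are. At ICC 0.05 that limits power to about 77% (normal) or 54% (4 df). At that ICC or above, 80% is out of reach without more clusters, which the article rules out.

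**Step 4: could the percentage analysis repair it?** The article does not define benefit, so the outcome is assumed normal, shifted by 0.495 SD in the intervention arm, and cut at a threshold. With 65 per arm and no clustering, the arcsine formula gives:

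- cut at 0 SD above the control mean (50% v 69%): 60%
- cut at 0.25 SD (40% v 60%): 61%
- cut at 0.5 SD (31% v 50%): 60%
- cut at 1 SD (16% v 31%): about 53%

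All fall below the 80% of the mean comparison under the same no-clustering conditions. If the analysis instead compares six cluster percentages, it respects the clustering but has 4 df, with about 41% power even at ICC 0.

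**The case against.** **The shortfall is disclosed.** The Weaknesses section names clustering as the cause and says that clusters cannot be added. That is true, and no reader is misled about the direction. But the disclosure carries no figure, stands apart from the sample-size section, and leaves 80% and the word sufficient unqualified there.

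**The percentage analysis is an addition.** A reader might infer that it lowers the trial's power. The article does not support that: the analysis is to be included alongside the comparison of changes, which stays, so it takes no power from it. Nor can one say that it must ignore clustering, because the wording allows summaries by cluster. What stands is narrower: under either reading it does not recover what clustering costs.

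**The 4-df test is not in the article.** The Statistical analysis section names t-test, Mann-Whitney and Chi2 tests with no cluster term. Run without adjustment, these would reject more often than the table shows, but with a true type I error of about 7%, 10%, 17% and 26% at ICC 0.01, 0.02, 0.05 and 0.10. That is not valid power. The objection does mean that the 4-df column describes a valid cluster-level analysis, not one the article has specified.

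**A one-in-two chance or less is not established.** A reader might draw that headline from the table. It needs either the 4-df test with ICC of about 0.01 or more, or an ICC of about 0.05 or more with the design effect alone. At ICC 0.01 to 0.02 the design effect alone leaves 66% to 73%. Nor does the article say that a non-significant result will be read as no effect; that is a risk, not a stated plan.

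**The magnitudes rest on unstated inputs.** SD, ICC, sidedness and the nursing-home split are all assumed. With SD 0.25 the individual calculation needs only 47 per group, so 65 would cover a design effect of about 65/47 = 1.4. The article's own admission makes such a hidden allowance unlikely. In addition, 0.145 is a difference in follow-up score while the primary outcome is change, so the relevant SD may differ.

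**Conclusion.** The point holds. The stated 80% belongs to an individually randomised trial of 130 and not to the six-cluster trial described; it survives only if ICC is zero and the analysis is at individual level. Under the stated assumptions, power for 0.145 is 73% to 36% for ICC 0.01 to 0.10 with the design effect only, and 50% to 24% with a cluster-level test (57% at ICC 0). The direction is firm, since the article concedes it. The exact sizes are a range and not an estimate.

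Unequal clusters or fewer of them would lower power further. On that, the Population section speaks of two nursing homes and the Randomization section of three nursing-home clusters; the two should be reconciled, because the calculation depends on the count.

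The percentage-that-benefits analysis does no harm to the mean comparison, but it is not a compensation for clustering.

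**What to change.** Keep the sample. Three text changes:

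1. In the sample-size section, replace the 80% figure and the word sufficient with the power, or the detectable difference, for six clusters over a stated ICC range (for example 0.01 to 0.10), and give the SD used.
2. State that conclusions will rest on the estimated difference and its cluster-adjusted confidence interval, and that a non-significant result will not be read as absence of effect.
3. In Weaknesses, drop the claim that the percentage analysis compensates; if it is kept, label it descriptive and report it by cluster.

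The cost is wording only: no extra participants, visits or procedures. The downside is that the stated power becomes less favourable.

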### Population, inclusion and exclusion criteria

Older adults (65+ years of age), receiving home-care or living in one of two nursing homes living in the Municipality of Frederiksberg, screened with EVS by the nursing staff caregivers and, according to the staff care givers are able to complete the planned tests.

Participants will be excluded from the study when they are not able or willing to give informed consent.

### Nutritional status

Participants are eligible for this study if they are identified with 2 points according to EVS
[9]. EVS contains information about eating habits, recent unintended weight loss, and the presence or absence of potentially modifiable nutritional risk factors (eating dependency, chewing and swallowing problems, acute disease, or acute change in chronic disease). The information is combined to give a total number of points, 0 point (no risk), 1 point (at risk), and 2 points (intervention).

### Control group

Before start of the intervention a nutrition education program will be performed educating selected staff members from the participating home-care and nursing homes to take the role as nutrition coordinator. The education of the nutrition coordinator includes three whole-day courses plus train-the-trainer sessions with other staff members (based on
[13]) and local study circles in-between (based on
[17]). These nutrition coordinators will be active in both the control and the intervention group. Also, in both groups standard interventions from physiotherapist, registered dietician and occupational therapist requested through the municipality’s normal assessment and referral system will be maintained.

**Figure 1 Fig1:**
[figure not shown]
**The new model for multidisciplinary nutrition support.**

#### Physiotherapist intervention

All participants in the intervention group will be offered to attend 30 to 45 min exercise program of moderate intensity twice a week. Focus will be on strength and balance exercises (based on evidence from
[12, 18]) supervised by physiotherapists affiliated to the study and with regular attendance by the caregivers. The program will be individualized according to the baseline assessment and performed in groups of five participants, or if not possible, individually in the participants’ own home. The program will start with a warm-up session with activities that involved large muscle groups. This will be followed by functional strength exercise of the upper and lower extremities and progressive dynamic balance training. The level of exercise will be evaluated regularly to ensure that the same relative training intensity will be maintained in terms of load, number of repetitions, exercise duration, and degree of difficulty in balance training.

The intervention group will receive one bottle (125 mL) of an oral “training” supplement immediately after the two weekly exercise bouts. The oral “training” supplement will provide an average of 1010 kJ and 14.4 g of protein per 100 mL twice a week and there will be different flavors to choose from. If a participant do not attend the group exercise, when possible the supplement will be offered anyway.

#### Registered dietician intervention

The registered dietician affiliated to the study will be asked to consult the participants in the intervention group with unintended weight loss according to the EVS or the weekly assessment of weight. To assess the dietary intake the registered dietitian will perform an interview with the participants and if necessary with help from the relatives or caregivers at the initial assessment. The nutritional support will be according to a treatment protocol and based on the official recommendations
[19]. The registered dietician will give the participants advice on how to raise the nutritional intake (i.e. consuming more dairy and whole-milk products, using butter and cream etc.), and discuss the importance of nutrition with participant, care givers and relatives (if possible). ONS and vitamin D and Calcium supplementation will be recommended as needed. The information will be supported by leaflets and an individual treatment plan made in collaboration with the participant.

The individual follow-up will be, in participant’s home, in the context of group exercise or by telephone. In addition, contact will be made to the caregivers, food service supplier, general practitioner, and others where appropriate. The time used for the initial assessment and follow-up will be documented.

